Recent evidence suggests that the autonomic system can be responsible for arrhythmogenesis and arrhythmia maintenance. Invasive approaches, such as stellate ganglion block and cardiac sympathetic denervation, have shown antiarrhythmic effects in patients with refractory ventricular arrhythmias (VA) [13–15]. Continuous vagal stimulation reduced VA and prevented sudden cardiac death in a canine model of post-myocardial infarction [16]. It is widely accepted that increased cardiac sympathetic activity plays an important role in the generation of VAs; suppression of cardiac sympathetic tone and/or stimulation of cardiac parasympathetic tone may have antiarrhythmic effects on VAs. Low-level tragus stimulation (LLTS) targets the auricular branch of the vagus nerve, an afferent nerve that relays information to central vagal projections in the brain stem. The signal is processed in the brain stem and higher centers, which in turn provide the efferent neural signal to the heart, which reaches the target organ via the vagus nerve. In addition to the scientific basis for the antiarrhythmic effect, previous clinical trials have supported that LLTS is a non-invasive and safe alternative for the treatment of atrial fibrillation [17, 18]. There have been at least two animal models have demonstrated the antiarrhythmic effect of LLTS on VAs induced by MI [19, 20]. Currently, the chronic effects of LLTS on VAs in humans remain unknown. Therefore, we designed a multicenter, double-blind, randomized, controlled trial between an LLTS group and a sham-control group, both receiving standard antiarrhythmic drug treatment, to: (1) assess the antiarrhythmic effects of LLTS on frequent PVCs in patients without SHD, (2) explore the possible mechanism of LLTS responsible for its antiarrhythmic effects, and (3) identify the potential responders to this novel therapeutic strategy.

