#### Inflammatory markers

Blood samples (10 ml) will be collected at baseline and at 3 and 6 months for measurement of inflammatory cytokines. The blood was then centrifuged to separate the serum and stored at − 80℃ in a refrigerator. Serum levels of inflammatory cytokines, including interleukin-1β, interleukin-6, and TNF-α, were measured using commercially available multiplex assays. All immunoassays will run in duplicate and read according to the manufacturer’s instructions. The investigators performing the cytokine assays will be blinded to group allocation.

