### Statistical plan

Descriptive statistics will be presented for baseline characteristics. Continuous variables are presented as mean ± SD or median (interquartile range), as appropriate. Categorical variables will be presented as proportions. Baseline variables will be compared between groups using Student’s *t*-test or Mann–Whitney *U* test for continuous variables and chi-square test for categorical variables. We will use a generalized estimating equation modelling approach to compare the outcome measure at the 3- and 6-month visits between the two groups after adjusting for the baseline measure [18]. Estimates reflect the exponentiated regression model terms and are interpreted as the ratio of the median responses in the active arm relative to the median response in the sham arm. Patients who discontinue the stimulation protocol and receive PVC ablation during the study period will be censored. These patients will be regarded as withdrawals from the study and the data from the last clinical follow-up will be included into final analysis.

Linear regression will be used to compare the association between the change in PVC burden at follow-up and measures of HRV and SKNA. Statistical significance will be set at *P* < 0.05 (two-sided). All statistical analyses will be performed using SAS software version 9.3 (SAS Institute, Cary, North Carolina).

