## Discussion

### Significance

TREAT PVC trial will contribute to the current literature at multiple levels. Clinically, it will be the first study to investigate whether LLTS can reduce the PVC burden in patients without SHD who suffer from frequent PVCs. LLTS may turn out to be a low-cost, minimal-risk, non-invasive alternative to antiarrhythmic or ablative treatment for these patients. Scientifically, the trial may shed new light on the mechanisms underlying the antiarrhythmic effects of LLTS. Previous literature supported the hypothesis that the antiarrhythmic effect of LLTS was attributed to its anti-adrenergic and possibly anti-inflammatory effects [17, 18]. To corroborate these hypotheses, we will collect data such as skin sympathetic nerve activity, heart rate variability, and inflammatory markers, such as interleukin-1β, interleukin-6, and tumor necrosis factor-α at baseline and during the treatment course, which may help elucidate the underlying antiarrhythmic mechanism. Additionally, these measurements will also help to clarify the correlation between autonomic perturbance and ventricular arrhythmias. Last but not least, these data will also help us to identify the responders to this neural therapy.

From the perspective of patients, the trial focuses not only on PVC burden but also on patients’ adherence and quality of life. As patient compliance is of paramount importance for the efficacy of the self-administrated treatment, it will be highly valuable to include the patients’ perspective in the development and evaluation of the intervention. A diary log and the SF-36 questionnaire will be introduced to assess the degree to which patients feel symptomatically improved by the intervention.

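### The regression linking PVC burden to HRV and SKNA states no term for arm or baseline burden and leaves out the cytokines, so a slope from it could not be read as evidence of a pathway

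*Protocol article*

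**What the plan says.** Background makes mechanism the second of three aims: to "explore the possible mechanism of LLTS responsible for its antiarrhythmic effects". The Significance section of the Discussion says that earlier literature saw the antiarrhythmic effect as "attributed to its anti-adrenergic and possibly anti-inflammatory effects", and continues: "To corroborate these hypotheses, we will collect data such as skin sympathetic nerve activity, heart rate variability, and inflammatory markers". The markers named there include interleukin-1β, interleukin-6 and TNF-α. These data are ones "which may help elucidate the underlying antiarrhythmic mechanism", and the section adds a purely correlational purpose: "these measurements will also help to clarify the correlation between autonomic perturbance and ventricular arrhythmias".

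The Statistical plan gives one sentence to the link between markers and burden: "Linear regression will be used to compare the association between the change in PVC burden at follow-up and measures of HRV and SKNA". It does not say which covariates enter, whether change is absolute, relative or logarithmic, whether the marker is a baseline value, a follow-up value or a change, or which visit is meant. The preceding paragraph describes a generalized estimating equation model to "compare the outcome measure at the 3- and 6-month visits between the two groups after adjusting for the baseline measure", with exponentiated estimates read as ratios. The Inflammatory markers section lists the cytokines as a secondary outcome, sampled at baseline, 3 and 6 months.

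**The concern.** Two features of the regression as worded can produce a slope with no pathway behind it.

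- **Shared treatment effect.** If stimulation lowers burden by one route and moves an autonomic marker by another, the arms differ on both. Pooling them without an arm term makes the two correlate even if they are unrelated within each arm. Stimulation moving both is close to the trial's own hypothesis.
- **Regression to the mean.** Change is follow-up minus baseline, so it is negatively related to baseline burden whenever the correlation between visits is below 1. A marker related to baseline burden then picks up a slope against change. This needs no treatment effect, and an arm term does not remove it.

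A third point is separate. The Discussion names two pathways, but the regression covers markers for only one. The anti-inflammatory pathway therefore has no stated link to PVC burden.

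At stake is how the mechanism aim is read. A significant slope could be taken as support for the anti-adrenergic pathway when the model alone produced it.

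**Working it through.** **The plan's own figures.** The article gives no figure for this regression. Sample size calculation gives 90 evaluable patients, two-sided α 0.05 and at least 80% power; 90 / (1 − 0.10) = 100 reproduces the recruitment target. No SD is given, so the 90 can only be inverted. With the article's noncentral F formula, N = 90 and equal arms, 80% power corresponds to a standardised difference of 0.597. A burden effect of 0.6 SD is therefore the size that the trial is built to detect.

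**Assumed inputs.** None of these is in the article: baseline/follow-up correlation 0.6 for burden and for marker, unit variances, and no marker-burden link within arm beyond the stated baseline correlation. The simulation used 45 per arm and at least 3,000 trials per setting. Each entry is the share of trials with P < 0.05 for the marker.

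**Case A: stimulation moves both, baselines uncorrelated.** Burden shifts by −0.6 SD.

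| Marker shift | Marker form | Marker alone | + arm | + arm, baseline burden, baseline marker |
|---|---|---|---|---|
| 0.3 SD | change | 7.5% | 4.9% | 5.6% |
| 0.6 SD | change | 14.7% | 4.4% | 4.6% |
| 1.0 SD | change | 32.7% | 6.8% | 5.6% |
| 0.6 SD | follow-up level | 13.9% | 5.4% | 5.8% |
| 1.0 SD | follow-up level | 27.0% | 5.4% | 4.4% |

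Repeat runs moved these by up to about two percentage points, so the range for 0.6 to 1.0 SD is about 13% to 33%.

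The cause can be checked by hand. The variance of change in burden is 2 − 2(0.6) = 0.8 within arm, plus 0.25 × 0.6² = 0.09 between arms, or 0.89 in total. With a marker shift of 0.6 SD, the variance of change in marker is also 0.89 and the covariance is −0.25 × 0.6 × 0.6 = −0.09. The pooled correlation is −0.09 / 0.89 = −0.10, although it is zero within each arm.

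**Case B: no treatment effect, marker correlated with burden at baseline.**

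| Marker form | Baseline correlation 0.3 | Baseline correlation 0.4 | Range over runs |
|---|---|---|---|
| Change | 8.3% | 11.5% | about 7–12% |
| Follow-up level | 11.9% | 16.9% | about 12–17% |
| Baseline level | 23.8% | 39.1% | about 23–40% |

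By hand, the covariance of change in burden with the baseline marker is −(1 − 0.6)r = −0.4r. At r = 0.3 the correlation is −0.12 / √0.8 = −0.13. For the follow-up level it is −0.4 × 0.6 × 0.3 / √0.8 = −0.08. For change in marker it is 0.4 × 0.4 × 0.3 / 0.8 = 0.06. The order matches the table.

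For the baseline marker, adding arm alone leaves 25.6% and 38.8%; adding baseline burden as well gives 4.8% and 5.2%.

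**Both together.** With a baseline correlation of −0.3, a burden shift of 0.6 SD and marker shifts of 0.3, 0.6 and 1.0 SD, change in marker rejects in 18.5%, 30.1% and 49.3% of trials alone, 8.6%, 8.8% and 8.5% with arm, and 4.3%, 5.0% and 5.0% with arm and baseline burden. With the follow-up level the two distortions pull in opposite directions: at a marker shift of 0.6 SD the unadjusted rate is 5.1%.

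**Neither condition.** If stimulation moves only one variable or neither, and baselines are uncorrelated, the unadjusted rate is 4.5% to 5.5%.

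**The case against.** - **Silence is not exclusion.** A reader might infer that the plan rules out arm and baseline terms and fixes change on the raw scale. It says neither. This is a condensed article, any analysis plan is not shown, and covariates and scale are often left to that plan. This stands, and makes the covariate point conditional on the regression being run as worded. It does not remove the point: the sentence does fix the method, the change outcome and the markers, and baseline adjustment is stated one paragraph earlier for another model.
- **Other mechanistic evidence remains.** A reader might infer that this regression is all that serves the mechanism aim. The markers are secondary outcomes, the HRV section says that HRV will be used to judge the effect on the autonomic nervous system, and the between-arm model can reasonably be read as covering them. A randomised comparison of each marker has neither distortion. This stands; the cytokines lack only a stated link to burden.
- **Only an association is promised.** The aim is exploratory and one stated purpose is correlational. This lowers the stakes, but the Discussion also ties the same data to corroborating the hypotheses.
- **The figures rest on assumptions.** This stands. The highest rates in Case B apply only to a baseline marker and should not be quoted for the model in general.

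**Conclusion.** The point holds in limited form. Read literally, the stated regression cannot tell a pathway from two separate effects of stimulation and is exposed to regression to the mean. The false-positive rate is about 13% to 33% for a shared effect of the assumed size. With no treatment effect it is about 7–12%, 12–17% or 23–40% for change in marker, follow-up level or baseline level, given baseline correlations of 0.3 to 0.4. All of this assumes a visit-to-visit correlation of 0.6. Where neither condition holds, the rate is nominal, so it would be wrong to conclude that the model generates false mechanisms in general.

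The cytokine gap is an inconsistency within the article and needs no assumption. A reader might link the two and infer that leaving out the cytokines helps to create a false HRV or SKNA finding. It cannot; it only leaves the anti-inflammatory pathway without a stated analysis against burden.

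The primary comparison is untouched. Priority is low to moderate.

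**What to change.** Replace the sentence with: *Month-6 log PVC burden will be regressed on the change in each marker (HRV, SKNA, IL-1β, IL-6, TNF-α), adjusting for baseline log burden, baseline marker and treatment arm; results will be reported as exploratory associations, not as proof of mechanism.*

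This settles the visit, the scale and the form of the marker, agrees with the ratio scale of the between-arm model, and brings the rejection rate back to about 5% in the settings examined. Arm alone is not enough, because it leaves the regression to the mean in place. The new model still does not identify mediation: the marker is measured after randomisation, so confounding and reverse causation remain, which is why the reporting clause is needed.

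All the data are already being collected. The cost is a few degrees of freedom.

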### Interim analyses

There is no plan for interim analyses.

### Methods for additional analyses

Subgroup analyses may be performed to determine which group of PVC patients is likely to respond to LLTS. Additional subgroup analyses, based on emerging research questions of interest, may be conducted as well.

### Methods in analysis to handle protocol non-adherence and any statistical methods to handle missing data

The analyses will be done in intention-to-treat population including all patients who received intervention or sham intervention without major protocol deviations. Significant protocol deviations or complications (hypotension, bradycardia, fainting, severe pain, and local infection) and subsequent failure to obtain primary and secondary outcome data will be documented prior the database closure. In case of withdrawals and missing data, the last observation carried forward procedure will be applied where appropriate.

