### Randomization and blinding

After baseline measurements have been collected, patients will be randomized 1:1 to active or sham LLTS using a central computerized randomization system to ensure blocked randomization. Sequence generation will be performed by an independent researcher through R, with a 1:1 allocation. To guarantee allocation concealment and to avoid selection bias, an independent researcher not involved in the trial will be charged to the custody of the sequences generated and to the allocation of the participants to each condition. Patients will not be informed of which stimulation site (tragus vs. earlobe) provides active stimulation. The investigators who assess the outcomes are also blinded to treatment allocation. The research coordinators who instruct the participant on ear clip placement according to randomized assignment and the study statistician are unblinded.

Unblinding can be performed at any time if participants experience an emergency. If necessary to ensure adequate treatment, where the principal investigator deems it necessary to identify the treatment, the investigator may perform unblinding and record the breach of blinding.

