#### Plans to promote participant retention and complete follow-up

The investigators will make every effort to improve participants’ adherence to follow-up and treatment by providing routine health care online or by telephone. All study patients, except those who withdraw consent, will be included in the analysis during the course of treatment.

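### The set labelled intention-to-treat leaves out untreated patients and undefined major deviators, and conflicts with two other rules on who is analysed

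*Protocol article*

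**What the plan says.** Three sections of the protocol article say who is analysed.

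- The section *Methods in analysis to handle protocol non-adherence and any statistical methods to handle missing data* defines the set as follows: "The analyses will be done in intention-to-treat population including all patients who received intervention or sham intervention without major protocol deviations". It adds: "In case of withdrawals and missing data, the last observation carried forward procedure will be applied where appropriate".
- *Plans to promote participant retention and complete follow-up*: "All study patients, except those who withdraw consent, will be included in the analysis during the course of treatment".
- *Statistical plan*, on patients who discontinue stimulation and have a PVC ablation: they are censored, and "These patients will be regarded as withdrawals from the study and the data from the last clinical follow-up will be included into final analysis".

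The primary comparison is in the *Statistical plan*: "We will use a generalized estimating equation modelling approach to compare the outcome measure at the 3- and 6-month visits between the two groups", adjusted for baseline. The article names only one analysis population, so the first definition governs that comparison. Under *Randomization and blinding*, "patients will be randomized 1:1 to active or sham LLTS" once baseline measurements are complete.

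**The concern.** An intention-to-treat set is fixed at randomisation. This one depends on two later events: whether the patient received stimulation, and whether a major protocol deviation occurred. Dropping only never-treated patients might pass as a modified intention-to-treat set. Dropping major deviators as well is what brings it close to per-protocol.

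Patients apply the treatment themselves twice a day for six months, and the article plans to measure compliance, so some non-adherence is to be expected. If the excluded patients differ between arms in number and in response, the arms compared are no longer those that randomisation created. The ratio for the primary outcome can then move in either direction. The label would also tell a reader that this risk had been avoided.

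The retention section gives a broader rule. Two analysts who each followed one section could analyse different patients and both claim to have followed the protocol.

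**Working it through.** The point rests on the text and not on a stated figure, so the first step sets the rules side by side.

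**1. Who is in the analysis under each section**

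| Randomised patient | Retention section | Non-adherence section | Statistical plan |
|---|---|---|---|
| Never stimulated, consent kept | in | out | silent |
| Stimulated, major deviation, consent kept | in | out | silent |
| Stopped stimulation, had ablation, consent kept | in | unclear: out if this counts as a major deviation | in, with last follow-up data |
| Stimulated, no major deviation, withdrew consent | out | in with the last value carried forward, if 'withdrawals' covers consent | silent |

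The first two rows are direct contradictions. The last two cannot be settled from the article, because it does not define 'major' and does not say which withdrawals it means.

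**2. How far selective exclusion could move the result**

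Inputs from the article: 50 patients per arm, two-sided alpha 0.05, a baseline-adjusted comparison, and an effect read as a ratio (hence the log scale). Inputs assumed because the article does not give them: SD of log burden 0.86, baseline correlation 0.7, no true effect, and excluded patients drawn at random from the half of their arm with the worse residuals.

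- Residual SD after baseline adjustment: 0.86 × √(1 − 0.7²) = 0.614.
- Mean residual in the worse half of a normal distribution: 0.614 × √(2/π) = 0.490.
- Removing k of 50 patients shifts that arm's mean log burden by −k × 0.490/(50 − k).

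Apparent ratio, active to sham:

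- 5 active, 0 sham: exp(−5 × 0.490/45) = exp(−0.054) = 0.95.
- 8 active, 0 sham: exp(−8 × 0.490/42) = exp(−0.093) = 0.91.
- 5 active, 3 sham: exp(−0.054 + 3 × 0.490/47) = exp(−0.023) = 0.98.
- 8 active, 5 sham: exp(−0.093 + 0.054) = exp(−0.039) = 0.96.
- 5 active, 5 sham: 1.00.

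Simulating the baseline-adjusted linear model under the same assumptions gives these ratios and the following type I error rates:

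| Removed (active/sham) | Ratio | Type I error |
|---|---|---|
| 0/0 | 1.00 | about 5% |
| 5/0 | about 0.95 | about 6.6% |
| 8/0 | about 0.91 | about 10% |
| 5/3 | about 0.98 | about 5% |
| 8/5 | about 0.96 | about 5% |
| 5/5 | 1.00 | about 4.3% |

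**3. Sample size**

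The planned 100 is 90/(1 − 0.10), which reproduces. That allows for 10% drop-out and makes no separate allowance for removing deviators.

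**The case against.** The strongest reply is that the set is not applied as a strict per-protocol set, and that little is known about whom it would exclude. Much of this stands, and it rules out several stronger readings that a reader might infer.

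- *That the analysis is simply per-protocol.* The *Statistical plan* keeps the last data of patients who discontinue and have an ablation, and withdrawals get the last observation carried forward. A strict per-protocol set would drop such patients. The accurate statement is that the three sections do not define one coherent set.
- *That changing drugs or stopping for discomfort counts as a major deviation.* The concomitant-care section says a change of medication is not prohibited. The section on discontinuing or modifying the intervention allows it for intolerable side effects or at the participant's request. Nothing classes either as a major deviation.
- *That patients with complications leave the primary set.* The sentence beginning "Significant protocol deviations or complications (hypotension, bradycardia, fainting, severe pain, and local infection" lists complications as an alternative to deviations and says only that these, and any resulting missing outcome data, are documented before the database closes. The exclusion itself names only major deviations.
- *That unblinded staff choose the exclusions.* The article says "The research coordinators who instruct the participant on ear clip placement according to randomized assignment and the study statistician are unblinded", but it does not say who classifies deviations.
- *That the false-positive rate will be 10%.* That figure needs eight exclusions from the active arm and none from sham. Sham patients follow the same self-administered schedule for the same six months, so zero sham exclusions is an extreme case. With removals in both arms the error rate stays near 5%, although a shift in the ratio remains when the numbers differ.

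The reply does not rescue the definition. The excluding sentence is explicit and carries a label that it contradicts. The retention section includes patients whom it excludes. A separate analysis plan or fuller protocol does not excuse this, because the article states the rule itself.

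**Conclusion.** The definition is wrong as written. It calls intention-to-treat a set that is close to per-protocol, leaves the deciding term undefined, contradicts the retention section and does not fit the ablation rule. This conclusion comes from the text alone and needs no assumption.

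The size of any bias is not known. Under the assumed log SD of 0.86 and correlation of 0.7, a spurious ratio would lie between about 0.91 (eight poorer responders removed from active only) and 1.00 (equal removals), with a type I error between about 10% and the nominal level or slightly below. These scenarios all remove poorer responders, with at least as many from active as from sham. Another pattern could shift the estimate the other way. The figures show what the rule permits and do not forecast what will happen.

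**What to change.** Replace the definition with wording such as: the primary analysis includes all randomised patients in the arm to which they were allocated, regardless of stimulation received or protocol deviations.

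Rename the present set per-protocol and use it only as a sensitivity analysis. Define a major deviation, and have deviations classified blind to allocation before the database closes.

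Bring the retention section, the *Statistical plan* and the non-adherence section to this one definition. In particular:

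- state how the censoring rule for patients who discontinue and have an ablation, and the carrying forward of last values, work within the all-randomised set, since a new population definition alone does not reconcile them;
- keep data collected before withdrawal of consent where the consent terms allow; those terms are not shown here.

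The cost is a change of wording, with the planned 100 patients unchanged. The estimate may become slightly less favourable. If the reconciled rules called for outcomes after discontinuation that are not now collected, that would cost extra follow-up.

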**Methods and design:**

The present study will be a prospective multicenter, double-blind, randomized, controlled trial to assess the antiarrhythmic effects of LLTS on frequent PVCs in patients without structured heart disease (SHD). A total of 100 patients with PVC burden > 10% will be randomly assigned to the active or sham LLTS in 1:1 fashion and receive the proposed intervention for 6 months. The primary outcome is PVC burden at 6 months as assessed by 10 days of continuous ambulatory electrocardiographic monitoring. Secondary outcomes include heart rate variability (HRV), quality of life, skin sympathetic nerve activity, and inflammatory markers. Adverse events will also be recorded.

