### Follow-up schedule

The planned follow-up period is 6 months, and two outpatient visits are scheduled at 3 and 6 months over this treatment duration. The assessments performed at each visit are displayed in Fig. 4.

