### Sample size calculation

Based on the 11 patients who underwent 1 month of stimulation, the average burden at baseline was 21.7% and the relative reduction after stimulation was 16.4%. We assume a baseline burden of 15% and expect a reduction of 40% at the end of 6 months. A sample size of 90 patients would provide at least 80% power to detect the specified effect sizes at a two-sided significance alpha level of 0.05. The sample size was calculated by using online statistic system (STATBOX, http://www.cnstat.org/statbox/; last access 9/19/2023). The exact formula used for sample size was as follows.$$1-{\varvec{\beta}}={\varvec{P}}{\varvec{\upgamma}}[{\varvec{F}}(1,{\varvec{N}}-2,{\varvec{N}}\{\left({{\varvec{\upomega}}}_{1}{{\varvec{\upomega}}}_{2}\right)[\frac{{{\varvec{\mu}}}_{1}-{{\varvec{\mu}}}_{2}}{{\varvec{\sigma}}}{]}^{2}\})\ge {{\varvec{F}}}_{\boldsymbol{\alpha }}]$$$${{\varvec{n}}}_{1}={{\varvec{N}}}^{\boldsymbol{*}}{{\varvec{\omega}}}_{1},\boldsymbol{ }{{\varvec{n}}}_{2}=\boldsymbol{ }{{\varvec{N}}}^{\boldsymbol{*}}{{\varvec{\omega}}}_{2}$$

To account for a potential drop-out rate of 10%, 50 patients in each group and 100 patients in total are planned to be recruited.

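### Carrying the last observation forward lets a month-3 or baseline PVC burden stand in as the month-6 primary result, which generally biases the treatment contrast

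*Protocol article*

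**What the plan says.** The abstract fixes the endpoint in time: "The primary outcome is PVC burden at 6 months as assessed by 10 days of continuous ambulatory electrocardiographic monitoring". The Follow-up schedule section provides few recordings that could be carried: "two outpatient visits are scheduled at 3 and 6 months over this treatment duration".

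The Statistical plan section gives the model, adjusted for the baseline measure: "We will use a generalized estimating equation modelling approach to compare the outcome measure at the 3- and 6-month visits between the two groups". Its estimate is "interpreted as the ratio of the median responses in the active arm relative to the median response in the sham arm", so the effect is a ratio.

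Two sentences deal with absent month-6 data:
- The section on non-adherence and missing data: "In case of withdrawals and missing data, the last observation carried forward procedure will be applied where appropriate". It gives no criterion for when this is appropriate and names no other method.
- The Statistical plan section, on patients who discontinue stimulation and undergo ablation: "These patients will be regarded as withdrawals from the study and the data from the last clinical follow-up will be included into final analysis".

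**The concern.** Last observation carried forward (LOCF) treats a patient's burden as frozen from the last recording onward. Here a patient lost after month 3 has month 3 entered twice. A patient lost before month 3 has only a baseline value. If that is carried, the same number is both covariate and outcome in the baseline-adjusted model. Either way the filled value enters as if it had been measured, so its uncertainty is ignored.

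The planned model does not need this. A model over months 3 and 6 can use a patient's month-3 recording with month 6 left absent. At stake is the primary estimate: a real effect may be diluted or, if the arms lose patients at different rates while burden falls in both, a difference may appear where none exists.

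**Working it through.** **Inputs from the protocol.** The Sample size calculation section has 90 evaluable patients, at least 80% power, two-sided alpha 0.05, 10% drop-out and 100 recruited. On effect size: "We assume a baseline burden of 15% and expect a reduction of 40% at the end of 6 months".

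**Assumptions not in the protocol.** These are the SD, the correlation between visits, the share lost before month 3, the size of the month-3 effect, any fall in the sham arm, and any imbalance in drop-out.

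**1. The plan's own figure.** 90 / (1 − 0.10) = 100, or 50 per arm. This reproduces. The 90 itself cannot be checked because no SD is given. Taking the difference as 15 × 0.40 = 6 points (sham flat) and solving the protocol's noncentral F formula, with noncentrality N × ¼ × (6/SD)², for 80% power at N = 90 gives an implied SD of 10.05 points and a standardised difference of 0.597.

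**2. Equal drop-out of 10%, sham flat, unadjusted protocol formula at N = 100.** Let the carried values hold a fraction c of the month-6 effect. The expected difference is 6 × (0.90 + 0.10c) and the expected ratio on the log scale is 0.60^(0.90 + 0.10c).

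| Carried values | c | Difference (points) | Ratio | Power |
|---|---|---|---|---|
| All baseline | 0 | 5.4 | 0.63 | 76% |
| Half baseline, half month 3 | 0.25 to 0.5 | 5.55 to 5.70 | 0.62 | 78% to 80% |
| All month 3 | 0.5 to 1 | 5.70 to 6.0 | 0.62 to 0.60 | 80% to 84% |

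The ranges for c assume that the month-3 effect is 50% to 100% of the month-6 effect. The SD is held unchanged. For comparison, 90 observed patients without imputation keep 6.0 points and 80% power.

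**3. No true effect, unequal drop-out, common fall.** If both arms fall to a proportion r of baseline, drop-out is qA (active) and qS (sham), and baseline is carried, the expected null ratio is r^(qS − qA). With 4% active and 16% sham the exponent is 0.12:
- 40% fall: 0.60^0.12 = 0.94
- 20% fall: 0.80^0.12 = 0.97
- 40% fall, month 3 carried, with 75% of the fall reached by month 3: 0.60^(0.12 × 0.25) = 0.98

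Type I error comes from simulation: 50 per arm, log SD 0.86, correlation 0.7 between visits, and loss completely at random within arm. A baseline-adjusted comparison at month 6 stands in for the planned model.

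| Case | LOCF ratio | LOCF type I error | Observed-data ratio and error |
|---|---|---|---|
| 40% fall, baseline carried, 4% active / 16% sham | 0.94 | about 8% (6.7% to 8.5% across runs) | 1.00, about 5% |
| Same, drop-out reversed | 1.06 | about 8% | 1.00, about 5% |
| 20% fall, baseline carried | 0.97 | 5.5% | 1.00, about 5% |
| 40% fall, month 3 carried | 0.98 | 4.9% | 1.00, about 5% |
| 40% fall, equal 10% drop-out | 1.00 | under 5% | 1.00, about 5% |

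**4. Power with baseline adjustment.** In the same simulation with a true ratio of 0.60 and equal 10% drop-out, all carried from baseline, the ratio moves to 0.63. Power is 97% with either LOCF or observed data. With a larger assumed log SD of 1.2 it is about 79% against 80%.

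**The case against.** - **Baseline carry is a reading, not a statement.** The LOCF sentence is qualified, and the ablation sentence speaks of follow-up data, which baseline is not. This stands in part. No text excludes baseline, and for a patient lost before month 3 there is nothing else to carry. The results are therefore given for both kinds of carried value.
- **The ablation sentence might mean only that data already collected are kept.** That is possible. But it classes these patients as withdrawals, and LOCF is the stated rule for withdrawals, so the two together lead to a carried month-6 value.
- **The larger figures rest on inputs that the protocol does not give.** This stands. A fourfold imbalance in drop-out with a 40% fall in both arms is an illustration, and milder inputs bring type I error back to about 5%.
- **With equal drop-out and a flat sham arm, LOCF is conservative.** This stands, but it does not protect against unequal loss. The Limitation section allows that patients may discover their allocation, which makes unequal loss possible.

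A reader might also infer that LOCF contradicts the plan's own expectation of a growing effect, 16.4% after 1 month against 40% at 6 months. The documents do not support this. The first figure was observed in 11 patients with a mean baseline of 21.7%; the second is a planning assumption from a 15% baseline. No trajectory and no month-3 expectation is stated.

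**Conclusion.** The concern holds as an avoidable source of bias in the primary estimate, and it should be fixed. At the planned 10% drop-out, equal between arms with a flat sham arm, the bias is modest: 0 to 0.6 of 6 points, toward no effect. Its direction is not assured when drop-out is unequal and burden falls in both arms.

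Two stronger conclusions are not supported. It does not follow that the planned power is missed: 76% arises only if every carried value is baseline under the unadjusted formula, and in the baseline-adjusted simulations power hardly changes. Nor is LOCF biased in every case of data missing completely at random. The bias vanishes, for example, if nobody leaves before month 3 and burden is stable afterwards. The protocol does not argue for that stability.

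All sizes depend on the assumed SD (about 10 points, or log SD 0.86), the visit correlation, the timing of loss and the common fall.

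**What to change.** 1. Delete the LOCF sentence in the section on non-adherence and missing data, and the last-follow-up sentence for ablation patients in the Statistical plan section. Removing only the first would leave a carry-forward rule in force.
2. Analyse observed log PVC burden at months 3 and 6 with arm, visit, arm-by-visit and baseline, by a method valid under missing at random: a likelihood-based repeated-measures model, or multiple imputation followed by the planned generalized estimating equation. Dropping LOCF and running that equation on observed data alone is not enough, because it generally needs data missing completely at random or depending only on the model's covariates.
3. State how recordings made after ablation enter the analysis.
4. Add one delta-adjusted (tipping-point) sensitivity analysis for patients without a month-6 recording.
5. Apply the same rule to the secondary outcomes.

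The cost is wording and some programming. No further data are needed.
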